#### Statistical analysis

2.5.2

The statistical analysis will have three phases. The first will consist of verifying that randomisation was effective in creating two comparable groups of schoolchildren, exploring the presence of extreme values and outliers, and assessing the degree of fit of the main variables to the normal distribution.

In the second phase, mixed regression models will be used, taking each outcome variable as the dependent variable, the intervention as a fixed effect (1 = IG and 0 = CG), adjusting for baseline values, age, sex, and including school (cluster) as a random effect. Given that this is a cluster-randomized trial, randomization is the main strategy to minimize selection bias, whereas covariate adjustment is intended primarily to improve precision and account for chance baseline imbalances. The results will be expressed as absolute differences in the changes in the variables between baseline and final measurements [95% confidence interval (95%CI)]. For binary outcomes (e.g., overweight/obesity), logistic regression models will be used, and odds ratios with their 95% CIs will be reported.

In the third phase, a sensitivity analysis will be performed to verify whether the results, using a different variable adjustment method, have the same direction and similar magnitude. To do this, the IG and CG will be compared using the propensity score statistical method to account for the imbalance of covariates in baseline measurements between clusters. The propensity score estimates the effect of the intervention using a causal inference model, explaining what would have happened if all subjects in the IG and CG had the same characteristics at the start of the study. Each subject is matched to a subject with similar characteristics using a caliper of 0.40 using the psmatch2 command.

All analyses will be conducted on an intention-to-treat basis, maintaining participants in their originally assigned IG or CG, regardless of the number of active-HIIT breaks they received, and considering the CONSORT recommendations for this specific type of cluster design (54). In addition to analyses for the total sample, subgroup analyses by age, sex, and socioeconomic status will be conducted.

However, to assess adherence to the intervention, data will be collected on the number of active HIIT breaks each group received. Children in classes that delivered ≥80% of the scheduled breaks will be considered to have received the intervention.

Results with a *p* < 0.05 will be considered statistically significant, and the analysis will be performed using the R and STATA18 statistical packages.

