**Methods:**

A RCT was conducted in nine schools in the province of Ciudad Real, Spain. Schools were randomly assigned to the MOVI-HIIT intervention group (*n* = 5) or the control group (*n* = 4). A total of 522 children aged 4–6 years were assessed at baseline (September 2022) and post-intervention (June 2023). The programme included two daily 6-minute HIIT-based ABs (20″/10″ work-to-rest ratio) guided by interactive avatars via a gamified digital platform. The primary outcomes were body composition, physical fitness, and executive function. Secondary outcomes included physical activity, sleep quality, blood pressure, and health-related quality of life. In parallel, a qualitative study using semi-structured interviews and focus groups examined teachers’ perceptions of barriers and facilitators related to the implementation and monitoring of the programme.

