### Design

2.1

This study protocol describes the MOVI-HIIT study, conducted as a two-arm RCT (ClinicalTrials.gov: NCT04863040), including an intervention group (IG) and a control group (CG). Ten schools from different municipalities in the province of Ciudad Real (Castilla-La Mancha region, Spain) were invited to participate. One school declined to participate, noting concerns about potential additional workload for teachers and limited digital skills; therefore, nine schools were included. After agreeing to take part, each school was randomly allocated to either the IG or CG using the StatsDirect statistical software (version 16). Five schools (two public rural, two public urban, and one private urban) were assigned to the IG, where the MOVI-HIIT programme was implemented, while four schools (two public rural and two public urban) were assigned to the CG, which continued usual school activities.

 Figure 1 illustrates the flowchart of the participant recruitment process. The effectiveness of the classroom-integrated MOVI-HIIT intervention was assessed in both groups at baseline and post-intervention.

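### The binary-outcome model is written without a school term, and the nine-school mixed model names no small-sample method; run literally, either could give p-values and intervals that are too optimistic

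*Protocol article*

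**What the plan says.** The Abstract (Methods) reports the allocation: "Schools were randomly assigned to the MOVI-HIIT intervention group (*n* = 5) or the control group (*n* = 4"). Section 2.1 (Design) explains that ten schools were invited and one declined; "therefore, nine schools were included". The Abstract also gives the number of children: "A total of 522 children".

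Section 2.5.2 (Statistical analysis) describes two model families in one paragraph. For the first, "mixed regression models will be used, taking each outcome variable as the dependent variable", with the intervention as a fixed effect, "adjusting for baseline values, age, sex, and including school (cluster) as a random effect". For the second: "For binary outcomes (e.g., overweight/obesity), logistic regression models will be used, and odds ratios with their 95% CIs will be reported". That sentence lists no school effect, baseline value or covariate.

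Later in the section, all analyses are to follow intention to treat, "considering the CONSORT recommendations for this specific type of cluster design (54"). The section closes by saying that results with p < 0.05 "will be considered statistically significant". It names R and Stata 18, but no estimation method (ML or REML), reference distribution or degrees-of-freedom method.

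**The concern.** Treatment was assigned to schools, so the evidence on its effect lies in the contrast between five school means and four. An analysis must allow for correlation within schools and for how poorly nine schools estimate the between-school variance.

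The two halves of the point differ in strength. For binary outcomes the text names a model, and that model lacks the school term that the preceding sentences give to continuous outcomes. For continuous outcomes the model is right for the design and the text is only silent on small-sample inference. With so few schools that silence matters, because a large-sample z test and a t test on 7 degrees of freedom can give clearly different answers. In both cases a default or literal analysis would err towards false positives and narrow intervals.

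**Working it through.** **Inputs.** Schools: 9, split 5 and 4 (Abstract; 2.1). Between-school degrees of freedom: 9 − 2 = 7. Children per school: 522 / 9 = 58. Section 2.5.1 (Sample size) says that the main analysis focuses on the half of children with the lowest baseline VO₂max, so 58 / 2 = 29 is shown as well. Level: 5%, taken as two-sided. The article gives no ICC, so 0.01, 0.02 and 0.05 are assumptions, to be read as residual ICCs after adjustment. The plan's only figure on this point is the nominal 5%, so there is nothing further to reproduce.

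**Binary outcomes, school ignored.** With m children per school and ICC ρ:

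- design effect DE = 1 + (m − 1)ρ
- type I error ≈ 2[1 − Φ(1.96/√DE)]
- interval width relative to the correct width ≈ 1/√DE

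| m | ρ | DE | Type I error | Relative width |
|---|---|---|---|---|
| 58 | 0.01 | 1 + 57 × 0.01 = 1.57 | 12% | 80% |
| 58 | 0.02 | 2.14 | 18% | 68% |
| 58 | 0.05 | 3.85 | 32% | 51% |
| 29 | 0.01 | 1 + 28 × 0.01 = 1.28 | 8% | 88% |
| 29 | 0.02 | 1.56 | 12% | 80% |
| 29 | 0.05 | 2.40 | 21% | 65% |

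This is a large-sample approximation. Simulating its linear-model analogue at m = 58 (school ignored, 20,000 trials per ICC) gave 11.7%, 18.1% and 31.8%.

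**Continuous outcomes, random intercept for school.** The critical value is 1.960 for z and 2.365 for t on 7 degrees of freedom; 2.365 / 1.960 = 1.21, so t-based intervals are 21% wider. ML also understates the between-school variance, because it divides the between-school sum of squares by 9 where REML divides by 7. Null trials with 5 and 4 schools of 58 children were simulated, with the between-school variance not allowed below zero and no covariates:

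| Assumed ICC | ML, z | REML, z | REML, t on 7 df |
|---|---|---|---|
| 0 | 4.4% | 3.8% | 1.4% |
| 0.01 | 8.4% | 6.6% | 3.2% |
| 0.02 | 10.6% | 8.0% | 3.7% |
| 0.05 | 12.4% | 9.0% | 4.6% |

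Separate runs of the z columns agree within 0.4 percentage points. As the ICC grows, the z-test error tends to P(|t₇| > 1.96) = 9.1% for REML and P(|t₇| > 1.96 × √(7/9)) = 12.8% for ML, whatever the school size. With 29 per school, REML with z gives 5.5% / 6.7% / 8.3% at ICCs of 0.01 / 0.02 / 0.05.

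**The case against.** On the continuous model the main objection is largely right. A random school effect with baseline adjustment suits this design. The choice of REML or ML, and of z or t, is commonly left to an analysis plan, which is not shown. Nothing in 2.5.2 says ML, z or 1.96, and a 5% threshold does not fix a reference distribution. A reader might infer that the plan rejects a small-sample correction and that its p-values will be too optimistic. The text does not support that; it states no method.

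On the binary model, the sentence follows directly after the full specification and does not repeat even the treatment term, so it may be shorthand that carries the school effect over. The reference to the CONSORT cluster recommendations covers all analyses and shows that the authors have clustering in mind. This makes the omission a reading of an ambiguous sentence, not an established error. It does not settle the matter, because the clause names no random effect, GEE or robust variance. The section is otherwise specific enough to fix a matching caliper and a software command.

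A reader might also infer that the error bars are wrong for every outcome. That goes too far. None of the primary variables in Table 1 is listed as binary; overweight/obesity appears only as an example in 2.5.2, and active versus inactive commuting is secondary. At ICC 0 the mixed model shows no inflation. The simulations also leave out the planned covariate adjustment.

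**Conclusion.** The point holds in conditional form. If the binary outcomes are analysed as written, without school, type I error would be about 12% to 32% over assumed ICCs of 0.01 to 0.05 with 58 children per school, and about 8% to 21% with 29. This is the stronger part, because a model is named and lacks the term that the design requires.

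For continuous outcomes the gap is an unstated method. A default z test would give about 6.6% to 9.0% under REML or 8.4% to 12.4% under ML over the same ICCs with 58 per school. Small-sample inference prevents this: with t on 7 degrees of freedom the error is about 3% to 5%.

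The number of schools and the missing school term come from the article. The size of the inflation depends on ICCs that it does not give, on equal school sizes and, for the continuous half, on which software default is used.

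**What to change.** In 2.5.2, or in the analysis plan if it is still open:

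- **Binary outcomes:** specify mixed-effects logistic regression with a school random intercept, adjusted for baseline status, age and sex, with a small-sample (t-based) reference for tests and intervals. The school term alone removes the error from ignoring clustering but still leaves a nine-school model that needs small-sample inference.
- **Continuous outcomes:** state that models are fitted by REML with Kenward-Roger or Satterthwaite degrees of freedom, and that p-values and confidence intervals are t-based.
- **Optional check:** a permutation test on the main outcome over the school allocations that the randomisation scheme allowed; unrestricted 5:4 allocation gives 9!/(5! × 4!) = 126.

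No new data are needed; the change is to wording and software options. The cost is intervals up to about 21% wider than z-based ones, and somewhat conservative tests when the ICC is very low (1.4% at ICC 0 for REML with t on 7 degrees of freedom).

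### The propensity-score sensitivity analysis pairs individual children under a caliper that does almost no work and states no school adjustment, so it is a weak check on the main model

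*Protocol article*

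**What the plan says.** Section 2.5.2 of the protocol article sets out three phases. Phase two is the main analysis: mixed models adjusted for baseline value, age and sex, "including school (cluster) as a random effect".

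Phase three is a sensitivity analysis. It asks whether the results, "using a different variable adjustment method, have the same direction and similar magnitude". The tool is the propensity score, used "to account for the imbalance of covariates in baseline measurements between clusters". The text adds that the score shows what would have happened had everyone in both arms started alike. The procedure is then fixed: "Each subject is matched to a subject with similar characteristics using a caliper of 0.40 using the psmatch2 command". The scale of the caliper is not given.

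The next paragraph covers every analysis: "All analyses will be conducted on an intention-to-treat basis, maintaining participants in their originally assigned IG or CG", whatever number of breaks they received, and "considering the CONSORT recommendations for this specific type of cluster design". The section ends with a general p < 0.05 threshold that does not exempt phase three.

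The abstract reports five intervention and four control schools, and says: "A total of 522 children aged 4–6 years were assessed at baseline".

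**The concern.** Three features of the stated procedure sit badly with its purpose.

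- **Caliper.** A caliper is meant to refuse poor matches. After randomisation, propensity scores cluster around the allocation fraction, so a distance of 0.40 on a 0-to-1 scale may refuse nothing.
- **Unit.** Schools were randomised and the imbalance of interest lies between schools, but the matching is child to child. The school term is named for phase two only. A matched comparison that treats children as independent understates its standard error.
- **Sample.** One-to-one pairing leaves some children out or uses some more than once. The matched estimate may then describe a different group from the whole of both arms, and the text does not say so.

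At stake is how the main result is vouched for. A matched estimate with intervals that are too narrow, on a different sample, could look like firm confirmation or like a contradiction when it is neither.

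**Working it through.** The plan gives no figure for this step other than the caliper, so there is no result to reproduce. The check is a simulation with no true effect.

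**Inputs from the article.** 9 schools (5 intervention, 4 control); 522 children; caliper 0.40.

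**Assumptions.**
- Equal school sizes: 522 / 9 = 58 per school, so 5 × 58 = 290 intervention and 4 × 58 = 232 control children. Per-arm counts are not in the text.
- Covariates: 3 or 10, with ICC 0 to 0.20.
- Outcome: 0.5 × first covariate + school effect + residual, with outcome ICC 0 to 0.10.
- 400 simulated trials per setting, logistic propensity score.

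**1. Does the caliper act?** The mean score is 290 / 522 = 0.56. Spread is the distance between the 1st and 99th percentiles of the score. Columns three to five give the share of intervention children with no control inside the caliper.

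| Covariates; covariate ICC | Spread of score | 0.40 on the score | 0.40 SD of logit | 0.20 SD of logit | All possible pairs allowed by 0.40 on the score |
|---|---|---|---|---|---|
| 3; 0 | 0.16 | 0% | 0.3% | 0.8% | 100% |
| 3; 0.05 | 0.30 | 0% | 0.4% | 1.0% | 99.7% |
| 10; 0.05 | 0.57 | 0% | 0.6% | 1.4% | 95.2% |
| 3; 0.20 | 0.51 | 0% | 0.8% | 1.7% | 94.8% |
| 10; 0.20 | 0.84 | 0% | 2.1% | 4.1% | 70.6% |

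On the score scale no intervention child lost its nearest match in any setting. Only under strong imbalance (last row) does 0.40 rule out a notable share of possible pairs: 100 − 70.6 = 29.4%.

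**2. What if school is ignored in the matched comparison?** The setting is 3 covariates, covariate ICC 0.05, nearest neighbour with replacement. The approximate false-positive rate is 2 × [1 − Φ(1.96 × naive SE / true SE)].

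| Outcome ICC | True SE | Naive SE | 1.96 × ratio | Approximate rate | Simulated rate |
|---|---|---|---|---|---|
| 0 | 0.121 | 0.131 | 2.12 | 3.4% | 3.3% |
| 0.02 | 0.157 | 0.131 | 1.64 | 10% | 9.8% |
| 0.05 | 0.199 | 0.131 | 1.29 | 20% | 20.7% |
| 0.10 | 0.254 | 0.130 | 1.00 | 32% | 32.8% |

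The Monte Carlo SE is about 1.5 to 2.3 points in the last three rows. Further runs with 5 covariates widen the ranges to about 7–12%, 17–27% and 26–38% at outcome ICC 0.02, 0.05 and 0.10. At outcome ICC 0.05, the other covariate settings gave 14.5% at the lowest (10 covariates, covariate ICC 0.20).

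**3. Who is in the matched set?**
- With replacement, 38.0% of controls were never used in the mildest setting and 51.6% in the strongest.
- Without replacement, at most 232 pairs can form, so at least 290 − 232 = 58 intervention children are dropped. The average reached 81 in the strongest setting.
- The loss comes mainly from pairing and the 5:4 allocation, so it is compatible with a caliper that excludes nobody.

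**The case against.** The strongest defence is that phase three compares direction and magnitude. Point estimates suffice for that, and no significance criterion is set for agreement. This stands in part: a reader might infer that the analysis cannot check the main result at all, and that goes too far. Intervals that are too narrow would still mislead if reported, and the general p < 0.05 rule does not exempt this step.

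A reader might also infer that matching breaks the intention-to-treat commitment. The documents do not support this. The rule as worded is about staying in the assigned arm whatever dose was delivered, and matching moves no child between arms. What remains is a point about sample and estimand.

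Nor does the text say that clustering is ignored. It is silent for this step, all analyses are said to consider the cluster CONSORT recommendations, and a fuller plan may give the details. The false-positive rates are therefore conditional on no school adjustment. The CONSORT clause names no method, so it does not settle the matter either.

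On the caliper, if scores lie close together then nearest neighbours are already similar, and little harm follows from a loose limit. Even 0.20 SD of the logit removes only 0.8–4.1% of intervention children. This is fair: the caliper is a safeguard that does little, not a demonstrated source of bias. Finally, the loss of 58 children needs matching without replacement and equal school sizes, and the article states neither.

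**Conclusion.** The point holds in a limited form. Phase three fixes child-to-child matching in a trial of nine randomised schools, with a caliper that is practically inactive on the score scale and nearly so on the logit SD scale. If school is not accounted for, the matched test rejects a true null at roughly two to seven times the nominal 5% or a little above (7–12% to 26–38%) over assumed outcome ICCs of 0.02 to 0.10. The matched set may leave out a large share of controls or the surplus intervention children, so it may not describe the whole of both arms.

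These sizes rest on assumed ICCs, equal school sizes, invented covariates and default matched standard errors. The result is a weak check on the main model. It is neither a useless one nor a breach of the intention-to-treat rule as worded. Severity is low to moderate, because the main model carries the school random effect and this step only supports it.

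**What to change.** Replace pair matching with propensity-score weighting of all children (overlap or inverse-probability weights), using covariates already collected. Base inference on schools with small-sample degrees of freedom, for example 9 − 2 = 7. This keeps a genuinely different adjustment method, as phase three intends, and uses every child with outcome data.

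If matching is kept:
- state the caliper on the logit scale and tighten it, for example to 0.2 SD;
- account for school in the matched analysis;
- say that the matched set and its estimand differ from the full-sample analysis, so that agreement is read as agreement in direction and rough size only.

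The cost is a change of wording and a little more analysis work. Intervals will be wider. No new data are needed, and the article says that intervention outcomes will be reported separately.

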## Discussion

3

This study was designed to address key challenges in promoting children's health: low levels of PA and high sedentary time among preschoolers, particularly during the school day (3, 4, 6). Although classroom-integrated PA has been associated with health and learning benefits, the evidence remains mixed and recent reviews highlight the need for more methodologically robust interventions, especially in preschool settings (10, 11, 17).

The MOVI-HIIT study was developed to help fill this gap by testing an AB–based HIIT intervention supported by a gamified digital platform. To our knowledge, it is the first programme of this kind in early childhood education to be evaluated in relation to body composition, physical fitness, and executive function. In addition, the nested qualitative study will explore teachers’ perceptions of barriers and facilitators to the implementation and monitoring, providing insights into real-world feasibility and scalability.

MOVI-HIIT extends previous AB research by incorporating a structured, high-intensity exercise, and digital delivery/monitoring component. Whereas most AB interventions in early childhood education have relied on unstructured or moderate-intensity activities (55, 56). MOVI-HIIT applies HIIT principles to brief sessions in a time-efficient format suited to preschoolers’ developmental characteristics. Previous studies implementing HIIT-based ABs programs in primary and secondary education have reported positive effects on physical fitness, body composition, and cognitive function (8, 57). However, to the best of our knowledge, no previous studies have implemented this type of intervention in early childhood education, and digital gamified delivery has rarely been examined in this context.

Therefore, the use of a gamified digital platform guided by interactive avatars represents a novel approach in this context, as it not only allows teachers to deliver sessions independently, supporting consistency, standardisation, and reproducibility across classrooms. In addition, the platform facilitates flexible integration of ABs within daily classroom routines. This technological integration aligns with emerging evidence that gamified digital tools can improve motivation, participation, and adherence in both educational and movement-based activities (20, 21).

Another strength of the MOVI-HIIT study lies in its rigorous methodological design. The RCT structure minimises contamination between groups while preserving the authenticity of the school environment, thereby enhancing external validity. Implementing the intervention within schools supports accessibility and scalability, as it can reach all children across diverse backgrounds. Moreover, previous evidence shows that increasing movement opportunities during the school day does not compromise academic performance, supporting the feasibility of integrating structured PA programmes into classroom routines (58). In addition, the use of validated and standardised instruments enhances measurement quality and comparability with previous studies. Finally, the nested qualitative component exploring teachers’ perceptions of barriers and facilitators will provide valuable insights into implementation processes, informing scalability and potential sustainability in real-world educational contexts.

Nevertheless, some limitations should be acknowledged. As with most behavioural interventions, blinding participants was not feasible, which may have introduced performance bias. Furthermore, variability in teacher motivation or classroom dynamics could affect programme fidelity; however, this was addressed through initial teacher training, ongoing technical support, and automated monitoring via the digital platform. Technical issues, such as temporary internet or power outages, could disrupt programme delivery; however, this risk was minimised by providing downloadable ABs and technical support staff from the research team. In addition, accelerometry in a subsample may limit the generalisability of findings related to PA and sleep, and data reported by parents may be subject to recall bias.

Additionally, although the trial included cognitive and adiposity outcomes, the sample size was estimated using VO_2_max as the reference outcome; therefore, the study may have had different statistical power across endpoints, particularly for outcomes with smaller expected effects.

Another limitation identified was that, although teachers were allowed to choose the timing of ABs to facilitate their implementation, the exact time of their implementation was not systematically recorded as a quantitative variable; therefore, possible differences according to the time of day could not be examined. Finally, the implementation of similar ABs in the control group was not formally monitored or objectively recorded; therefore, some degree of contamination could not be completely ruled out.

In conclusion, the MOVI-HIIT study presents an innovative and potentially scalable model for integrating HIIT-based ABs into preschool classrooms through a gamified digital platform. By detailing the prespecified methods and implementation strategy, this article aims to support transparency and reproducibility, and to inform future school-based interventions. The study will provide insights into the potential effects of HIIT-based ABs on body composition, fitness, and executive function, alongside teachers’ perspectives on implementation, which may help guide future educational practice and health policy to foster active and healthy school environments.

